#### Business Logic Engine for My Asthma Target and Alerts

##### Patient Alerts

The first line of feedback to patients is generated automatically from the MAP database system (Figure 2) using monitoring information entered by the participant and information from the EHR system. The business logic for the color-coding and advice presented to patients is summarized in Table 2. An alert is sent to patients via email when the system identifies that a participant's asthma is poorly controlled and the participant indicates they have not initiated use of their action plan, if the nurse has updated the action plan, or if they have not logged in for 7 days (Table 3). The participant is given an opportunity to act on these alerts and if the flag of a problem for any of these areas remains for 48 hours, the alert status is escalated to notify the nurse case-manager.

**Table 2 T2:** Monitoring business rules

	Green	Yellow	Red
Symptoms	No symptoms	1 symptom	2 symptoms and/or emergency visit

Overuse of rescue puffer*	P < 150	250 > P ≥ 150	*P *≥ *250*

Adherence to preventative medication#	n/d ≥ 90%	90% > n/d > 70%	n/d < = 70%

Exercise†	number steps ≥ average	number steps > 2/3 of average	number steps < 2/3 of average

Action Plan Understanding%	"Yes" to all questions	N/A	"No" to at least one question

* (P = number of puffs corresponding to all FABA and combivent dispensed over last 3 months)

# (quantity dispensed/3 months) [144]

† Calculated once exercise monitoring questionnaire is completed 4 or more times (average is the mean value for the first three entries, × = the last steps entry)

%Action Plan questions: do you understand what to do in your action plan?; Are you able to describe the signs or symptoms you have when your asthma is getting worse?)

**Table 3 T3:** Alerts to Patients and Nurse Case Manager

Event or trigger	Alert to patient	Alert to nurse
**Patient Not logging into MAP**	Emails sent at 7 days and 14 days since the last log-in to the patient.	Alert to nurse at 21 days since the last log-in.

**Asthma Out of Control (OOC) and Action Plan Use**		

Patient OOC and action plan not started:	Email to patient within 24 hours of OOC status detected	Nurse receives alert "AP not started" alert (after 48 hrs) If patient starts action plan: Patient turns yellow in case management patient list and stays yellow for 14 days.

Nurse updates action plan of a patient:	Email to patient and pop-up when patient logs-in	

Patient indicates not understanding action plan		Nurse receive alert and contacts patient

Add/change medication: Patient adds or changes medication in asthma target questionnaire		Nurse receives "create/review action plan" alert If it is the patient's first entry of medication the alert is an "Initial drug list" alert

Preventative medication monitoring		Increase or decrease of intake triggers alert to nurse

Rescue medication monitoring: FABA, oral corticosteroid		Increase triggers alert to nurse

Discrepancy in medication detected: Discrepancy between what is prescribed and what is dispensed	After 1 week an email is sent to the patient	After 2 weeks an alert is sent to the nurse

Change in medication detected: Physician enters change through MOXXI for patient's asthma medication		If, when the patient fills out the monitoring questionnaire, patient does not update medication change, an alert is sent to the nurse

##### Nurse Alerts

Upon receiving this notice, the nurse follow-ups with the participant within 24 hours through the MAP mail system or by telephone. Additional alerts are sent to the nurse when a new participant is enrolled and needs to have their action plan reviewed, the participant indicates that he/she does not understand his/her action plan, or there is a change in the way a participant is taking their medication based on the medication adherence monitoring assessment (Table 3).

### Measurements

#### Participant Demographics

Demographic information such as participant sex, age, and indicators of social economic status (e.g. household income) will be abstracted from baseline questionnaires.

### Primary Outcomes

**Asthma control **will be evaluated by examining overuse of rescue fast acting bronchodilators (beta2-agonists) (FABA) (i.e. participants will be classified as overused yes/no). Excessive use of rescue fast acting bronchodilators was included as an indicator because it is associated with an increased risk of hospitalization and death from asthma [110], and is defined as the dispensing of more than 500 doses of the most commonly prescribed fast acting beta2-agonist salbutamol 100 mcg, 2 inhalations at the time, or the equivalent for other fast acting bronchodilators in the last six months of follow-up. Doses dispensed will be based on quantities recorded in dispensed prescriptions from the RAMQ and private pharmacy prescription files. The maximum acceptable use of fast acting beta2-agonists is derived from recommendations in the guidelines that allow up to 3 doses per week and a daily dose for the prevention of exercise induced symptoms [51]. Previously developed methods will be used to adjust quantities dispensed for prescriptions filled before and immediately before the end of the item window for assessment [111].

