### Sample Size

The primary outcome for this study is change in asthma control. We hypothesized that use of MAP would be associated with a 10% reduction in the proportion of patients classified as being in poor control. Based on MOXXI-II results, we have estimated that 19% of asthma patients will either be seen in the ED for respiratory-related problems, or use greater than 500 doses of fast-acting beta2-agonists in a 6-month period. Thus the intervention would need to reduce the proportion of asthmatics in poor control to 9% to be considered to be sufficiently effective for policy and practice adoption.

Thus, to detect a 10% difference in proportions, [140] with 80% power using a cutoff for statistical significance of 0.05, the sample size needed is 67 participants in total. To account for attrition and loss to follow-up, we will recruit an additional 13 subjects for a total of 80 participants, and 40 participants per arm [141].

This sample size will also allow us to detect a minimal important difference of .5 on the AQLQ [113,142], using the Mini-AQLQ a difference as large as 0.97 (SD .61) was found to be clinically meaningful and significant [114,143-145].

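### The unit of the primary-endpoint cut-off is inconsistent by a factor of about two: 500 'doses' fits its own derivation only if a dose there means a single inhalation

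*Protocol article*

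**What the plan says.** Three places in the protocol article bear on the cut-off.

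- **Primary Outcomes.** Each participant is classified as overusing rescue medication, yes or no. Overuse is "dispensing of more than 500 doses of the most commonly prescribed fast acting beta2-agonist salbutamol 100 mcg, 2 inhalations at the time". Use of other rescue bronchodilators is converted to an equivalent, and the window is the final six months. The paragraph then gives the origin of the maximum acceptable use: guidelines that "allow up to 3 doses per week and a daily dose for the prevention of exercise induced symptoms".
- **Patient Alerts, Table 2 (monitoring rules).** The row on overuse of the rescue puffer is yellow from 150 to below 250 and red from 250 upwards, where "P = number of puffs corresponding to all FABA and combivent dispensed over last 3 months".
- **Sample Size.** The planning rate is introduced with "we have estimated that 19% of asthma patients will either be seen in the ED for respiratory-related problems". The other way to count towards that rate is to "use greater than 500 doses of fast-acting beta2-agonists in a 6-month period". No number of inhalations per dose is given there.

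Under Statistical methods, the proportions in and out of control, judged by doses dispensed, are compared between arms with a chi-square test.

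**The concern.** The cut-off and its derivation stand in the same paragraph and both use the word 'dose', but they differ by about a factor of two if the word means the same thing in both. Table 2 counts puffs, and its red level also corresponds to about half of the literal cut-off. The article never says whether the 500 counts single inhalations or two-inhalation administrations.

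The dichotomy is the primary outcome. Two analysts working from this text could convert dispensed quantities to doses with divisors of 1 and 2. They would then disagree on every participant dispensed 501 to 1,000 inhalations. If the unit were settled only after the dispensing data had been seen, choosing the unit would amount to choosing the endpoint.

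**Working it through.** **Inputs**
- Cut-off: more than 500 doses, two inhalations at a time, in six months (Primary Outcomes).
- Stated basis: 3 doses a week plus 1 a day (Primary Outcomes).
- Red level: 250 puffs or more in 3 months (Table 2).
- Window: six months, taken as 26 weeks.

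**Step 1: the plan's cut-off from its stated basis**
- Doses per week: 3 + 7 = 10.
- Over 26 weeks: 10 × 26 = 260 doses.
- At two inhalations per dose: 260 × 2 = 520 inhalations.
- Taking six months as 182.6 days instead gives 260.9 doses, or 521.7 inhalations.

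The stated 500 doses is not reproduced.

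**Step 2: the cut-off read literally**
- 500 × 2 = 1,000 inhalations.
- 500 / 26 = 19.2 doses a week.
- 1,000 / 182 = 5.5 inhalations a day.

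**Step 3: comparison with the basis**
- 500 / 260 = 1.92.
- The number of inhalations per dose cancels, so this ratio holds for any value as long as 'dose' has one meaning in the paragraph.

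**Step 4: comparison with Table 2**
- Red level over six months at constant use: 250 × 2 = 500 puffs.
- Literal cut-off against the red level: 1,000 / 500 = 2.0.
- Table 2 against the stated basis over 13 weeks: 10 × 13 × 2 = 260 puffs, and 250 / 260 = 0.96. These two nearly agree.

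**Step 5: the other reading, 500 single inhalations**
- Against the stated basis: 500 / 520 = 0.96.
- Against the red level: 500 / 500 = 1.0.

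| Reading of the 500 | Inhalations in six months | Ratio to stated basis (520) | Ratio to red level (500) |
|---|---|---|---|
| Two-inhalation doses | 1,000 | 1.92 | 2.0 |
| Single inhalations | 500 | 0.96 | 1.0 |

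**Step 6: who is affected**
- Dispensed 501 to 1,000 inhalations: overused if the 500 counts single inhalations, not overused if it counts two-inhalation doses.
- Dispensed 521 to 1,000 inhalations: above the plan's stated maximum, yet not overused on the literal reading.
- Dispensed 501 to 520 inhalations: the classification differs between readings, but the stated maximum is not exceeded.

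**The case against.** The strongest reply is that this is loose wording and not a doubled cut-off. The text can be read as 500 inhalations of 100 mcg, usually taken two at a time. On that reading the cut-off is close to the 520 inhalations of the derivation and equals the Table 2 red level. Taking the count from dispensed quantities also fits a count of single units. This stands. A reader might infer that the threshold is 1,000 inhalations and that overuse will therefore be misclassified; the article states neither, and its own figures sit at least as well with single inhalations. But that reading needs 'dose' to mean one inhalation in the cut-off sentence and two in the derivation. The reader has to repair the text, which an endpoint definition should not require.

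Table 2 is a feedback rule for portal users, not an endpoint definition. It also counts Combivent, uses 'at least' where the endpoint uses 'more than', and covers 3 months. It need not equal the endpoint cut-off, and doubling it assumes constant use. This stands too, but the 1.92 within Primary Outcomes does not rest on Table 2.

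A reader might also infer that the event rate and the power shift by a calculable amount. The documents do not support that. The 19% combines emergency visits with overuse, the share due to overuse alone is not given, and no distribution of dispensed quantities is reported. If planning and analysis count in the same unit, the planning rate need not move at all. Any single cut-off also applies equally to both arms, so the ambiguity does not by itself bias the comparison.

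Finally, a condensed article may leave conversion details to the full protocol. That would excuse silence, but here the cut-off and its basis are both stated and disagree. The earlier methods that the paragraph cites adjust for when prescriptions are filled relative to the assessment window, and are not described as fixing the unit.

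**Conclusion.** The point holds as an inconsistency of unit. Applied literally, the primary-outcome rule is 1.92 times the maximum from which it is said to derive, and 2.0 times the Table 2 red level at constant use. Counted in single inhalations, it is 0.96 and 1.0 times those figures. The 1.92 assumes only that 'dose' has one meaning within the paragraph and that six months is about 26 weeks. The 2.0 also assumes two inhalations per dose and steady dispensing.

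It is not established that the cut-off is 1,000 inhalations, that anyone will be misclassified, or that the planning rate or power is wrong on this account. Which cut-off is right is not judged here. The text should still be corrected before outcome data are extracted, because the choice of reading decides who counts as a primary event.

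**What to change.** Before any outcome data are extracted:

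1. State the cut-off in Primary Outcomes in one unit, such as salbutamol 100 mcg-equivalent inhalations per six months, and say how dispensed quantities are converted to it.
2. Reconcile that figure with the weekly and daily allowance in the same paragraph, with the 500 doses in Sample Size, and with the puffs in Table 2. If the Table 2 rule is meant to differ from the endpoint, say so.
3. Confirm that the overuse part of the 19% taken from MOXXI-II was counted in the same unit, noting that the 19% also includes emergency visits.

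Classifying participants under the other reading as a sensitivity analysis is optional. The cost is one definition, matching wording in two other places and one check of the planning source. No new data are needed.

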#### Asthma Quality of Life

The Mini-Asthma Quality of Life Questionnaire (Mini-AQLQ) was developed to measure the four functional impairments that are most important for adults (symptoms, emotions, exposure to environmental stimuli and activity limitation) [112,113]. It has 15-items measured on a 7-point Likert scale. The Mini AQLQ is widely used in asthma clinical trials because it has good internal consistency (interclass correlation coefficient = 0.83), and a strong cross-sectional correlation with the 32-item AQLQ of 0.9), and moderate level correlation of 0.69 (both cross-sectional and longitudinal correlation) with the Asthma Control Questionnaire [112,114], and it is sensitive to change (reliability index = 0.97) [112].

### Secondary Outcomes

#### Acceptability and attitudes toward the web portal

The Technology Acceptance Model (TAM) [115-127] questionnaire will be used to assess acceptability and attitudes toward the web portal. The instrument was found to be reliable and valid (convergent, discriminant) for measurement of perceived ease of use and usefulness [121,123,128-130]. Reliability coefficients range from 0.92 to 0.98 for perceived usefulness and 0.88 to 0.94 for perceived ease of use [121,128]. Perceived usefulness and ease of use were significantly correlated with both self-reported current usage (r = .63, r = .45) and self-predicted future usage (r = .85, r = .59) in two different populations (users within IBM Canada's Toronto Development Laboratory, evening MBA students at Boston University) [129].

Usage rates of the system will also be assessed by examining automated audit trails (logs), which will include the frequency of use defined as the number of minutes patients spent logged into the system/week. Patterns of usage will include the number of days/week and times that patients logged in, and which features of the system they used including number of messages sent to the asthma nurse. Additional open-ended questions will be asked to receive further feedback about the usefulness of the system and how it fits with individuals' self-management practices.

**The Chronic Disease Self-Efficacy Scale **[131], has been shown to have adequate psychometric properties in patients with chronic arthritis and several conditions including hypertension, diabetes, congestive heart failure, recent myocardial infarction, major depression, and/or depressive symptoms [132] and was adapted to assess asthma self-efficacy. The test-retest and the internal consistency reliabilities were respectively 0.77 and 0.97 in an asthma patient population [133]. In the chronic arthritis population, items for test-retest reliabilities ranged from 0.71 to 0.85; all the correlations for construct and concurrent validity were significantly different from zero (p < 0.01): r = -0.35 to -0.68 for baseline self-efficacy with baseline health status, r = -0.32 to -0.68 for baseline self-efficacy with 4-month health status, r = -0.48 to -0.73 for 4-month self-efficacy with 4-month health status; r = 0.61 for concurrent validity (perceived performance and actual performance) [131]. Patients rate their level of confidence, 1 = not confident at all, 10 = very confident. Level of confidence will be rated with respect to: taking medications as prescribed; items that are behaviour-specific related to recognition and appropriate management of deteriorating asthma symptoms including ability to identify signs of deterioration and need to initiate the prescribed action plan; capacity to keep a healthy diet; ability to do exercise or physical activity on a regular basis.

#### Medication Adherence

Adherence to controller asthma medications will be evaluated by comparing medications prescribed to medications dispensed based on the prescription claims in the RAMQ system. This will be calculated using validated methods we developed to adjust quantities dispensed for prescriptions filled before and immediately before the end of the time window for assessment [111].

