**Methods:**

The trial is a parallel multi-centered 2-arm pilot randomized controlled trial. Participants are randomly assigned to one of two conditions: a) MAP and usual care; or b) usual care alone. Individuals will be included if they are between 18 and 70, have a confirmed asthma diagnosis, and their asthma is classified as not well controlled by their physician. Asthma control will be evaluated by calculating the amount of fast acting beta agonists recorded as dispensed in the provincial drug database, and asthma quality of life using the Mini Asthma Related Quality of Life Questionnaire. Power calculations indicated a needed total sample size of 80 subjects. Data are collected at baseline, 3, 6, and 9 months post randomization. Recruitment started in March 2010 and the inclusion of patients in the trial in June 2010.

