### MAP linked to a nurse-case management system

#### Initial set up and information exchange

Three systems are linked together, MAP, the nurse case-management system, and a light MOXXI electronic health record (EHR). The EHR contains drug information entered by the physician and from the Quebec provincial health database (RAMQ) including: 1) medications prescribed by the physician, and the RAMQ record for all drugs dispensed, medical services provided, ED visits and hospitalizations. Relevant data from the EHR are sent to MAP and the nurse case-management system. The MAP system also provides links to selected patient educational materials from credible online resources.

Participants are given a MAP username and password and are asked to access the internet from anywhere (home, work, library). They are asked to select the number of times they will commit to logging in per week, with a minimum log in of at least 1×/week. During the first time log in, they complete a *My Profile *page to verify basic demographic information, enter additional health information (e.g., smoking status, allergies, triggers) and select initial health goals to work on.

Once patients complete the initial log-in, their information appears in the nurse case management system. When the nurse receives a new participant file, she reviews the accuracy of the medication list, the action plan details, and clarifies discrepancies with the referring physician, if needed. As patients complete monitoring information in the MAP system (symptoms, medication adherence, action plan use, and physical activity), the information appears simultaneously in the nurse case-management system. Based on information from the EHR and participant responses to patient reported outcomes in MAP, the MAP and nurse case-management systems provide clinical decision support (described later on) to patients and the nurse. The flow of information between MAP and the other systems is presented in Figure 2.

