#### Health care Utilization

Asthma-related ED visits or hospitalizations will be abstracted from provincial database (RAMQ) using validated algorithms [134] which lists information on the date, type, provider, and location of service delivery (e.g. inpatient, emergency, clinic) for all medical services remunerated on a fee-for-service basis (approximately 86% of all services) [135].

Resource Utilization: "Information on the time spent by the nurse case manager (type of call, who is making the call, duration and reason) will be recorded, and will allow us to address health service research issues and knowledge translation to other practitioners and health care organizations. All health-care resources used during the 6-month follow-up will be considered. Intervention costs will include resources used to develop the web-based tool, train patients and nurses to use the system, administer the intervention (time spent for research data collection will not be included). Real time spent with each patient will be carefully documented by each study case manager. Case manager salary costs will be estimated based on the average pay scale of the Federation of Nurses of Quebec. Physician fees will be based on those set by the Provincial Health Insurance Board [136]. "Healthcare utilisation": Information from the provincial health insurance program administrator, RAMQ, will be obtained on asthma-related ER visits or hospitalizations. Total cost per ED visit will be based on data from earlier studies conducted in the province of Quebec [137,138]. ED visit will be a separate resource item from hospitalization. Hospitalization costs will be based on a Quebec index called the Niveau d'Intensité Relatif des Ressources Utilisées (NIRRU)" [139].

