#### Study Timeline

Recruitment started in March 2010 and the inclusion of patients in the trial in June 2010. Follow-up evaluations are conducted at 3 months, 6 months, and 9 months after randomization.

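### Controller adherence is taken from RAMQ claims alone although the primary outcome adds private pharmacy files for the same patients; separately, the 6-month resource window is not reconciled with 9 months of follow-up

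*Protocol article*

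**What the plan says.** **Dispensing source.** Four places in the protocol article bear on this.

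- Medication Adherence defines controller adherence by "comparing medications prescribed to medications dispensed based on the prescription claims in the RAMQ system". It mentions no second source.
- Primary Outcomes, on fast-acting beta-agonist (FABA) use, says: "Doses dispensed will be based on quantities recorded in dispensed prescriptions from the RAMQ and private pharmacy prescription files".
- The Abstract describes the same FABA outcome by the amount "recorded as dispensed in the provincial drug database", without the private files.
- The section on initial set-up and information exchange says the electronic record draws on "the RAMQ record for all drugs dispensed, medical services provided, ED visits and hospitalizations".

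The inclusion criteria ask for age, diagnosis, a prescribed rescue drug, poor control, internet access, a smoking limit and language. Public drug coverage is not among them.

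**Resource window.** Health care Utilization, in its resource paragraph, says: "All health-care resources used during the 6-month follow-up will be considered". Study Timeline says: "Follow-up evaluations are conducted at 3 months, 6 months, and 9 months after randomization". The FABA threshold in Primary Outcomes applies to 500 doses of salbutamol "or the equivalent for other fast acting bronchodilators in the last six months of follow-up".

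**The concern.** Adding private pharmacy files to the FABA outcome makes sense only if RAMQ claims miss some fills. A patient whose rescue inhaler is dispensed outside RAMQ may well have the controller dispensed outside RAMQ too. Under the adherence definition as written, that controller would appear as prescribed but without a matching dispensing record, and a prescribed-versus-dispensed comparison can read this as non-adherence.

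The missing-data provision in Statistical methods does not obviously catch this. It offers multiple imputation as a sensitivity analysis, but an unrecorded fill can enter the data as a zero rather than as a missing value. Adherence is also named there as a potential effect modifier in the regressions on the primary outcome, so an error in it would reach those exploratory models as well as its own arm comparison.

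The resource window is a separate and smaller matter. The text speaks of a 6-month follow-up in a trial that follows patients for 9 months, and it does not say which six months are meant.

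**Working it through.** The plan states no figure on this point, so there is none to reproduce. The check sets the sections side by side and then shows how the consequence scales.

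**1. Sources compared**

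| Outcome | Section | Source |
|---|---|---|
| FABA doses (primary) | Primary Outcomes | RAMQ and private pharmacy files |
| FABA doses (primary) | Abstract, Methods | Provincial database only |
| Controller adherence (secondary) | Medication Adherence | RAMQ claims only |

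Two dispensing outcomes in the same patients have different sources, and no reason is given.

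**2. If uncaptured fills count as zero**

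Let q be the share of patients whose controller fills all lie outside RAMQ. The documents do not give q, so 10%, 30% and 50% are assumptions. True mean adherence of 60% is also an assumption, taken as the same in captured and uncaptured patients.

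Apparent mean = true mean × (1 − q):

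- q = 0: 0.60 × 1.0 = 0.60, no effect
- q = 10%: 0.60 × 0.9 = 0.54
- q = 30%: 0.60 × 0.7 = 0.42
- q = 50%: 0.60 × 0.5 = 0.30

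With the same q in both arms, a true difference between arms shrinks by the same factor (1 − q).

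**3. If those patients are set to missing instead**

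The planned size is a "total of 80 participants, and 40 participants per arm". Evaluable patients = 80 × (1 − q), before other attrition. The standard error grows by 1/√(1 − q):

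- q = 10%: 72 patients, factor 1.05
- q = 30%: 56 patients, factor 1.20
- q = 50%: 40 patients, factor 1.41

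The loss is then one of precision, without the attenuation in step 2.

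**4. Chance imbalance in coverage**

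Randomisation is stratified by centre only. Treating coverage as binomial in each arm, at q = 30% and 40 per arm, the standard deviation of the between-arm difference in private share is √(2 × 0.3 × 0.7 / 40) = 0.10. With zero-coding and 60% true adherence, this adds noise of about 0.60 × 0.10 = 0.06, or 6 percentage points (one standard deviation), to the adherence difference. Its expectation is zero.

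**5. Resource window**

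Six of nine months is 6/9 = 67% of follow-up time. Months 0–6 would not match the primary outcome's window; months 3–9 would, taking follow-up to end at month 9. The text supports neither reading over the other.

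**The case against.** The case on the other side is substantial, and much of it stands.

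- **No rule for uncaptured fills.** Nothing in the article says that patients without RAMQ claims are scored zero. The figures in step 2 therefore illustrate one possible handling and do not describe a planned one. It remains true that the adherence source, as written, omits files that the primary outcome uses.
- **RAMQ may be complete.** The set-up section describes the RAMQ record as covering all dispensed drugs. If so, q is 0 and nothing is lost. But Primary Outcomes, the operative definition, adds private files and so points the other way.
- **Confounding by insurance mix.** A reader might infer that the arm comparison is biased. The documents do not support this: allocation is randomised, so coverage is balanced in expectation. Attenuation or noise is the realistic harm.
- **The primary outcome.** A reader might infer from the Abstract that missing FABA claims would pass as good control. The Abstract line is a condensation, and Primary Outcomes governs. Only the wording needs aligning.
- **Lost events.** A reader might infer that a third of emergency visits and hospitalisations is discarded. The sentence defining that outcome states no window; the 6-month phrase stands in the costing paragraph. The one third is follow-up time and not a known share of events.
- **Lost set-up costs.** A reader might infer that a window of months 3–9 drops training costs. Intervention costs are listed in a separate sentence with no window, and they include building the tool, which precedes follow-up altogether.
- **Weight.** Adherence is a secondary outcome in a pilot. Costs are not among the Objectives, and the Discussion leaves their examination to future work. A window applied equally to both arms is not in itself a measurement error.

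**Conclusion.** The point holds in a limited form. The adherence outcome, as written, leaves out a dispensing source that the plan itself considers necessary for the primary outcome, in patients who need not have public drug coverage. Fills outside RAMQ would be uncaptured and could be read as non-adherence.

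The size cannot be fixed from the article. It ranges from nothing at a private share of 0% to a fall from 60% to 30% at a share of 50%, and the latter rests on three assumptions: zero-coding, the share itself and the true adherence level. That is enough to justify a change, but it does not show that adherence will in fact be mis-measured.

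The resource window carries less weight. The 6-month phrase conflicts with the 9-month schedule and has no start or end. It needs clarifying and is not shown to distort a comparison. Neither matter undermines the primary analysis as defined in Primary Outcomes.

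**What to change.** 1. In Medication Adherence, compute controller adherence from the same RAMQ and private pharmacy files as the FABA outcome. This assumes that the private files hold controller fills, which the article does not say. If they do, the cost is wording and some data handling; if they do not, the file request must be widened, or the difference in source explained.
2. State that a patient with no captured dispensing source is missing and not zero. A patient who is captured but filled nothing remains a genuine zero. The existing multiple-imputation sensitivity analysis can then cover the missing cases.
3. Align the Abstract's description of the FABA source with Primary Outcomes, and check the set-up section's description of the RAMQ record against it. This is a wording change only.
4. Give the resource window in Health care Utilization a start and an end. Randomisation to 9 months in both arms would use all of the follow-up, at the small cost of a longer claims extract. If the primary outcome's six-month window is preferred, say so and give the reason.

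All four are best settled before the claims data are extracted.
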